### Qualitative data

We would like to evaluate the acceptability of these devices among clinicians who may use and recommend them and patients who may wear them for extended periods. We will aim to recruit 15–25 individuals who do not have AF and provide them with the wearable devices to evaluate for prolonged use, and will also interview between 10 and 15 GPs and practice nurses. Purposive sampling will be applied to ensure broadly similar representation of men and women and individuals from urban and rural settings. Semistructured interviews will be conducted using focus groups with digitally recorded, transcribed verbatim and identifiable data removed for ethical reasons. Inductive thematic analysis of each transcript will be carried out. Deviant case analysis will be used to ensure that perspectives that diverged from dominant trends are not overlooked.

The initial coding structure will be revised to develop a coding manual based on consensus among the research team. This will result in a robust conceptual overview of the factors that influence patients to use the various AF monitors being evaluated and whether they can be self-applied and used for continuous periods of 24 or 48 hours reliably and with comfort. This will allow us to understand the pragmatic issues around the use of each of the appliances and will substantively influence further evaluation of this equipment for the detection of AF in primary care. It will allow us to address our feasibility objectives and translate this study into more definitive and patient centred recommendations about the use of this equipment in the community. It will also allow us to understand the issues that may face clinicians in primary care when recommending the use of this equipment to screen and diagnose.

### Statistical analysis

We will collect baseline data including age and gender. We will document the sensitivity and specificity with their 95% CIs. We will also test whether the specificity is significantly greater using the bespoke algorithm by comparing the proportions using the χ^2^ test. The gold standard will be ECG diagnosis of AF by a panel of three cardiologists. The ECGs will be analysed in batches in order that new AF diagnoses are conveyed during the trial. If a subject is not known to have pre-existing AF and is diagnosed by ECG as having AF, we will send a copy of the ECG to the GP and also inform the patient and include a patient information leaflet on treatment options.

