#### Sample size

If we assume the specificity of the new algorithm is between 97% and 99%, to detect a difference in specificity compared with the other devices of 5% (ie, 97% vs 92%; 98% vs 93% or 99% vs 94%) requires 329 individuals who do not have AF for 80% power and α of 0.05. Assuming the sensitivity of the devices using the bespoke algorithm is 95% to 99% then 73 individuals with AF are needed to estimate the sensitivity to within ±5%. A recent study found the AliveCor automated algorithm to have a specificity of 99.4% but a relatively low sensitivity of 71.4% and it may be that AliveCor have modified their algorithm.^26^ In this case, we would expect to detect a significant difference in sensitivity between AliveCor and the new algorithm.

We aim to recruit known AF patients (from GP records) to reduce the population size required (although some of these patients may have reverted to sinus rhythm or have paroxysmal AF) and also patients not known to have AF who will represent a typical screening group with a low prevalence. Assuming that 20% of patients coded as AF in the GP records will have paroxysmal AF or not be in AF when they attend, we will increase the numbers in this group accordingly to 92. We also aim to recruit AF and non-AF patients at the same rate and to have the ECGs coded in batches and therefore we can stop recruiting patients with pre-existing AF when we have achieved more than 73 patients coded as AF on their ECG. We will include further subjects not known to have pre-existing AF who are subsequently diagnosed on their ECG.

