#### Randomisation

The four devices will be tested on each participant in a random sequence. The sequences for each participant will be generated by the trial statistician.

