#### Procedures/study schedule

The study will be conducted by Good Clinical Practice (GCP) certified researchers. Participants will have an AF detection screen using four devices in randomised order (Polar H7 belt with bespoke algorithm; second wearable device (Firstbeat Bodyguard 2), WatchBP, AliveCor). A randomisation code will be generated by the trial statistician for each participant and list the order to test the devices (eg,1. Polar H7, 2. AliveCor, 3. WatchBP, 4. Firstbeat Bodyguard 2). The time taken for the testing is likely to be around 30–40 min. Although some patients with paroxysmal AF may experience changes in heart rhythm during the visit, we did not want to subject the study population to multiple ECG recordings and single ECG recordings have been used elsewhere.^29^ The ECGs will be reviewed by a panel of three cardiologists as to whether AF is present. The study visit is depicted in figure 1.

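### The specificity comparison is planned with an ordinary χ² test although every device is read on the same participants; a paired test should be named

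*Protocol article*

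**What the plan says.** The design is within-participant. The Randomisation section says "The four devices will be tested on each participant in a random sequence", and Procedures/study schedule repeats it: "Participants will have an AF detection screen using four devices in randomised order". The same section records one overall AF or not-AF classification per device.

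The Statistical analysis section plans sensitivity and specificity with 95% CIs for each device, and then adds one hypothesis test: "We will also test whether the specificity is significantly greater using the bespoke algorithm", to be done "by comparing the proportions using the χ^2^ test".

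The Sample size section sizes the non-AF group "to detect a difference in specificity compared with the other devices of 5" percentage points, with 97% against 92%, 98% against 93% and 99% against 94% as the cases. It states that this "requires 329 individuals who do not have AF for 80% power and α of 0.05".

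The article does not mention pairing, McNemar's test, discordant results or within-person correlation.

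**The concern.** The usual χ² test for two proportions treats them as coming from separate groups. Here each AF-free participant contributes a result to both proportions. The variance of the difference then depends on how often the two devices give a false positive in the same person, and the ordinary χ² test ignores this.

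Some overlap is plausible, since all devices judge the rhythm of the same person at one visit. With positive overlap the χ² standard error is too large. The p-values are then too high, and a true advantage of one device is harder to show than the data allow. This is the only test named in the analysis section, and the non-AF group is sized on it.

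**Working it through.** **Inputs.** From the Sample size section: 329 people without AF, specificities 97% and 92%, α = 0.05, power 80%. Two-sided testing is assumed, because it reproduces the stated number and a one-sided calculation gives 257. The overlap of false positives is not in the article. It is varied below as the share of the better device's false positives that the other device also shows.

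**1. Reproducing 329.** The unpaired formula (pooled, no continuity correction) is

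n = [1.96·√(2p̄(1−p̄)) + 0.8416·√(p₁(1−p₁)+p₂(1−p₂))]² / δ², with p̄ = 0.945 and δ = 0.05.

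This gives [1.96·√0.10395 + 0.8416·√0.1027]² / 0.0025 = 326. The continuity-corrected version gives 365.

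The paired (McNemar) formula, with ψ the proportion of discordant participants, is

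n = [1.96·√ψ + 0.8416·√(ψ−δ²)]² / δ².

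With independent errors, ψ = 0.08×0.97 + 0.03×0.92 = 0.0776 + 0.0276 = 0.1052. This gives [1.96·√0.1052 + 0.8416·√0.1027]² / 0.0025 = 328.

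Both results are close to 329, so the stated number does not show which formula was used. The pairs 98/93 and 99/94 need fewer (269 and 211, unpaired), so 97/92 drives the size.

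**2. Type I error of the unpaired test on paired data, both specificities 95%.** The χ² test assumes n × variance of the difference = 2×0.05×0.95 = 0.095. The true value is 2×0.05 − 2×(proportion false positive on both). With 50% shared it is 0.10 − 0.05 = 0.05, a ratio of 0.05/0.095 = 0.526. The test then rejects only when the correctly scaled statistic exceeds 1.96/√0.526 = 2.70, which has a two-sided probability of about 0.7%. Simulation (multinomial, n = 329, at least 200,000 draws) agrees:

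| False positives shared | χ² type I error | McNemar type I error |
|---|---|---|
| never | 5.6% | 5.0–5.1% |
| independent | 5.0% | 5.1% |
| 25% | 2.8% | 5.3% |
| 50% | 0.75% | 4.9–5.0% |
| 75% | 0.02–0.03% | 4.4% |

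**3. Simulated power, 97% against 92%, n = 329** (both tests without continuity correction), with the number needed for McNemar's test by formula:

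| Shared | χ² power | McNemar power | McNemar n for 80% |
|---|---|---|---|
| never | 82% | 80% | 343 |
| independent | 82% | 82% | 328 |
| 25% | 84% | 87% | 296 |
| 50% | 86% | 93% | 249 |
| 75% | 89% | 98% | 202 |

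**4. A smaller difference.** For 97% against 94% (assumed; not a planning case in the article), with 50% shared, power is about 46% for χ² and 63% for McNemar.

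**The case against.** - **The wording does not exclude a paired test.** McNemar's statistic is also referred to a χ² distribution, and 329 fits a paired calculation as well as an unpaired one. This stands as a caution about what the authors intended. As written, however, comparing proportions with the χ² test describes the unpaired test, and nothing points to a paired one. The article names a method, so this is more than a detail left to an analysis plan. If McNemar's test was meant, naming it still corrects the text.

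- **Overlap of false positives is not documented.** Table 1 shows that the comparators use an ECG trace and a peripheral pulse, against RR intervals for the bespoke algorithm. The readings are also taken one after another. This stands, which is why a range is shown. With independent errors the two tests perform alike.

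- **The test errs on the safe side and the trial keeps its power.** This stands at the planned difference. A reader might infer that the stated 80% power is missed, but the uncorrected χ² test stays above it at every overlap examined. A reader might also infer that false claims for the bespoke algorithm become more likely. The type I error exceeds 5% only slightly (5.6%), and only when false positives never coincide.

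- **Pooling the two bespoke devices.** A reader might take the single phrase for the bespoke algorithm to mean that Polar H7 and Firstbeat readings will be combined, counting each person twice. The article does not plan this: Objectives, Outcomes and Procedures treat them as separate devices.

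**Conclusion.** The concern holds in a limited form. The named test does not match the paired design, and it has its nominal 5% level only if the devices' false positives are independent within a person. Under positive overlap it is conservative. At 50% shared, its type I error is about 0.75% instead of 5%, and its power at 97% against 92% is 86% where a paired test would have 93%. The loss is efficiency and calibration, and it grows in importance if the true difference is smaller than 5 points.

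These figures rest on an assumed overlap, two-sided testing and no continuity correction. Each device's own sensitivity and specificity with 95% CI are unaffected, and 329 remains adequate for a paired test unless false positives hardly overlap (343 by formula if they never do). The point is one that should be fixed; it does not invalidate the trial.

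**What to change.** In the Statistical analysis section, replace the χ² test with McNemar's test, using the exact version when discordant pairs are few, and state in advance when that applies. The choice matters somewhat: at 97% against 92% the exact version has about 77% power with independent errors and 89% with 50% shared, against 82% and 93% for the uncorrected version. About 35 discordant pairs (0.1052 × 329) would be expected under independence.

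Report the paired difference in specificity with a 95% CI for Polar H7 and for Firstbeat, each against WatchBP and AliveCor.

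In the Sample size section, state the discordance assumed behind 329. Independent errors (10.52% discordant) give 328, so the number can stand.

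The cost is one sentence in each section, with no extra participants, visits or data.

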## Discussion

The SAFETY trial will be one of the first trials to directly compare two existing AF screening devices (with NICE recommendation) within the same trial. In addition, this will be the first trial to evaluate inexpensive wearable consumer devices that can be used for prolonged monitoring and directly compare these with both existing AF detection devices and gold standard 12-lead ECG. Importantly we will also collect quantitative and qualitative data from the trial participants to evaluate the suitability of the devices. We have chosen participants aged 65 and above as this will yield a higher prevalence of previously undetected AF and the over 65s are at higher risk from AF-related stroke. In addition, we will gain insights from GPs regarding AF screening including their opinions on the devices, and wider issues such as workload. Based on the results, we will aim to design a larger trial to investigate prolonged AF screening in the community using inexpensive consumer devices.

Trial Status

We began recruitment in November 2016.
